## Abstract

**Introduction:**

Cognitive impairment is present in the majority of individuals with first-episode psychosis (FEP) and is a strong predictor of long-term functional disability. Despite this, evidence-based cognitive interventions are rarely available in routine mental healthcare in low-income and middle-income countries, where most young people with psychosis reside. This protocol describes the CognIFied study, a pilot randomised controlled trial evaluating the feasibility and acceptability of a culturally adapted, task-shifted compensatory cognitive training (CCT) intervention for young adults with FEP in Nigeria.

**Methods and analysis:**

CognIFied is a multicentre, assessor-blind, parallel-group pilot randomised controlled trial with an embedded mixed-methods process evaluation. The study will recruit 180 young adults aged 18–30 years with Diagnostic and Statistical Manual of Mental Disorders, Fifth Edition (DSM-5)-defined FEP (onset within the past 5 years) and objective cognitive impairment from three public psychiatric hospitals in Nigeria. Participants will be randomised 1:1 to receive either culturally adapted CCT or an active control condition, Enhanced Recreational Therapy. Both interventions comprise 12 weekly group sessions lasting 60–90 min. CCT is delivered by trained psychiatric social workers using a manualised curriculum co-designed with young people with lived experience. Primary outcomes assess feasibility (recruitment, retention, intervention adherence), acceptability (Client Satisfaction Questionnaire-8) and intervention fidelity. Secondary outcomes include preliminary signals of effectiveness on global cognitive functioning (Brief Assessment of Cognition in Schizophrenia) and functional capacity (University of California, San Diego [UCSD] Performance-Based Skills Assessment), assessed at baseline and at 3, 6 and 12 months. Quantitative analyses will be descriptive and exploratory, supplemented by qualitative inquiry guided by Reach, Effectiveness, Adoption, Implementation, Maintenance (RE-AIM) and Consolidated Framework for Implementation Research frameworks and an exploratory economic evaluation.

**Ethics and dissemination:**

Ethical approval has been obtained from relevant institutional review boards. Findings will be disseminated through open-access publications, policy-focused stakeholder engagement and community dissemination co-led by a Youth Research Team.

**Trial registration number:**

ISRCTN44794154.

STRENGTHS AND LIMITATIONS OF THIS STUDYThis multicentre pilot randomised controlled trial employs an assessor-blinded, parallel-group design with allocation concealment using sequentially numbered opaque sealed envelopes, stratified by site and age group.The inclusion of an active control condition structurally matched on session number, duration, group size and facilitator contact minimises confounding from non-specific therapeutic factors.An embedded mixed-methods process evaluation, guided by the RE-AIM framework and Consolidated Framework for Implementation Research, enables systematic examination of implementation mechanisms alongside quantitative feasibility outcomes.Independent fidelity monitoring of a random 20% sample of audio-recorded sessions, using a structured adherence and competence checklist, provides an objective index of task-shifted delivery integrity.As a pilot feasibility study, the trial is not powered to detect definitive effects on clinical outcomes, and preliminary estimates of effectiveness should be interpreted with caution.

## Introduction

### Background and Rationale

 Psychotic disorders typically emerge during late adolescence and early adulthood, a critical period that often determines long-term functional trajectories.^1^ First-episode psychosis (FEP), defined as the presentation with full-threshold psychotic symptoms within the preceding 5 years, occurs with a substantial estimated incidence (34 per 100 000 persons annually).^2 3^ While hallmark positive symptoms, such as hallucinations and delusions, remain the focus of acute psychiatric intervention, they do not constitute the sole, or even the most robust, determinant of long-term recovery and community integration.^4^

A considerable body of evidence consistently indicates that cognitive impairment is a core, enduring feature of FEP, affecting more than 75% of individuals even at first presentation.^5^ These deficits traverse multiple domains, including verbal learning and memory, processing speed, executive functioning, attention and social cognition.^6 7^ Such impairments may frequently predate the onset of full-threshold symptoms and persist during symptomatic remission, robustly predicting long-term functional disability, such as unemployment and social isolation, more reliably than the severity of positive or negative symptoms.^7 8^ Consequently, enhancing cognitive functioning is increasingly recognised as a rate-limiting step in achieving holistic recovery.

### The treatment gap in low-income and middle-income countries

Approximately 80% of young individuals experiencing FEP reside in low-income and middle-income countries (LMICs), contexts where the duration of untreated psychosis is often prolonged and resource constraints are severe.^9^,^11^ In Nigeria, routine care for FEP commonly concentrates almost exclusively on pharmacological symptom stabilisation using antipsychotic medication.^12^ Although antipsychotics are essential, their efficacy in mitigating cognitive deficits is limited, and high doses may, in fact, exacerbate these issues due to anticholinergic burden.^13^,^15^ Structured cognitive interventions are virtually absent from public-sector psychiatric services, leaving the primary driver of functional disability unaddressed and contributing to a complex ‘double burden’ of biological illness and structural exclusion from socioeconomic opportunities.^10^

### Compensatory cognitive training: a pragmatic solution

While cognitive remediation is an established component of comprehensive psychosis care in high-income settings,^16 17^ traditional restorative approaches often rely on expensive computerised drills and specialised neuropsychological staff, posing a substantial barrier to scalability in resource-limited environments.^16^ Compensatory cognitive training (CCT) offers a pragmatic and low-cost alternative. Instead of attempting to restore underlying neural deficits through repetitive practice, CCT uses a ‘prosthetic’ model, teaching manualised, behavioural strategies to circumvent cognitive weaknesses.^18 19^ Participants are trained to employ external aids (eg, calendars, alarms, notes) and internal strategies (eg, mnemonics, self-talk) to efficiently manage daily tasks.^20^ Meta-analytic evidence supports the efficacy of CCT in improving functional outcomes and quality of life.^17 19^ Its manualised curriculum and suitability for group delivery position it as a strong candidate for implementation in LMICs.^17^

### The need for adaptation and task-shifting

Despite CCT’s promise, transferring Western-developed interventions directly into new cultural contexts carries the inherent risk of ‘voltage drop’; a diminished effectiveness resulting from poor cultural fit.^21^ Differences in daily cognitive demands, family structures, literacy levels and illness explanatory models necessitate rigorous cultural adaptation.^22 23^ Furthermore, the severe shortage of mental health specialists in Nigeria necessitates innovative delivery models. Task-shifting, the redistribution of tasks to non-specialist health workers, is an established WHO-endorsed strategy designed to bridge this workforce gap.^24 25^

### Study rationale

The CognIFied study aims to address these implementation challenges by systematically adapting CCT for the Nigerian context and evaluating a delivery model reliant on task-shifting to psychiatric social workers. To our knowledge, no prior trial has evaluated a culturally adapted cognitive intervention for FEP in West Africa.^25 26^ This pilot randomised controlled trial employs a Youth Participatory Action Research (YPAR) methodology to ensure the intervention is co-designed with young people.^27 28^ Ultimately, the study seeks to generate essential data on feasibility, acceptability, implementation fidelity and preliminary clinical signals, which are requisite steps for informing the design and powering of a future definitive trial.^29 30^

### Study aims and objectives

The overarching aim of the CognIFied study is to evaluate the feasibility, acceptability and preliminary clinical signals of a culturally adapted, task-shifted CCT intervention for young adults with FEP in Nigeria, compared with an active control condition. In line with international guidance for pilot trials, the primary emphasis is placed on determining whether the intervention can be delivered with adequate fidelity and sustained engagement within existing public mental health service infrastructure, rather than on hypothesis-driven tests of efficacy.

#### Primary objectives: feasibility and acceptability

**Objective 1 (Feasibility):** To assess the feasibility of recruiting and retaining young adults with FEP into a longitudinal cognitive intervention trial across three public psychiatric hospitals. It is anticipated that recruitment of 180 participants within a 9-month enrolment period will be achievable, corresponding to the recruitment of at least 60% of eligible individuals screened. Retention of at least 70% of randomised participants at the 12-month follow-up is expected. Among participants allocated to CCT,^19^ it is anticipated that at least 75% will attend a minimum therapeutic dose, defined as nine or more of the twelve sessions.**Objective 2 (Acceptability):** To evaluate the acceptability of the culturally adapted CCT intervention among service users and facilitating staff. Acceptability will be operationalised through participant satisfaction scores, with the expectation that mean scores on the Client Satisfaction Questionnaire-8 (CSQ-8)^31^ will reach or exceed 24 out of a possible 32 at the 3-month assessment.**Objective 3 (Fidelity):** To determine whether CCT can be delivered with adequate fidelity and competence by non-specialist health workers within a task-shifted model. It is anticipated that trained psychiatric social workers will achieve at least 80% adherence to manualised content and delivery competence benchmarks, based on independent coding of a sample of audio-recorded sessions.

#### Secondary objectives: preliminary effectiveness

**Objective 4 (Clinical signals):** To estimate preliminary effects of CCT,^19^ relative to Enhanced Recreational Therapy (ERT),^32^ on global cognitive functioning and functional capacity over a 12-month follow-up period. Participants receiving CCT are expected to demonstrate greater improvements on the Brief Assessment of Cognition in Schizophrenia^33^ composite score and the UCSD Performance-Based Skills Assessment (UPSA-N),^34^ although these analyses are exploratory in nature.**Objective 5 (Broader outcomes):** To explore potential effects on real-world disability, psychiatric symptom severity and quality of life, generating effect size estimates to inform future trial design.

#### Exploratory objectives: implementation and economics

**Objective 6 (Process evaluation)**: To examine implementation processes and contextual influences on delivery, adoption and sustainability using the RE-AIM framework,^35^ complemented by qualitative inquiry with key stakeholders.**Objective 7 (Economic evaluation)**: To generate preliminary data on resource use and delivery costs, enabling an exploratory cost–consequence analysis to inform future scale-up considerations.

## Methods

### Study design

The CognIFied study is designed as a multicentre, assessor-blind, parallel-group pilot randomised controlled trial (as illustrated in figure 1), with a 1:1 allocation ratio. The trial is complemented by an embedded mixed-methods process evaluation and a preliminary economic evaluation, reflecting its dual emphasis on clinical feasibility and implementation readiness. The overall design is informed by the UK Medical Research Council framework for the development and evaluation of complex interventions^36^ and is reported in accordance with the Standard Protocol Items: Recommendations for Interventional Trials 2013 guidelines^37^ and the Consolidated Standards of Reporting Trials (CONSORT) extension for pilot and feasibility trials29 (see table 1, Checklist File 1 and 2).

**Figure 1 F1:**
[figure not shown]
CONSORT flow diagram for the CognIFied pilot randomised controlled trial. CCT, compensatory cognitive training; CONSORT, Consolidated Standards of Reporting Trials.

**Table 1 T1:** SPIRIT schedule of enrolment, interventions and assessments

Study period	Screening	Baseline (T0)	Randomisation	Intervention period	3 months (T1)	6 months (T2)	12 months (T3)
Enrolment							
Eligibility screening (MINI 7.0)	✓						
Cognitive screening (BACS)	✓						
Informed consent	✓	✓					
Demographics and clinical history		✓					
Random allocation			✓				
Interventions							
CCT (12-weekly group sessions)				✓			
Enhanced recreational therapy (12-weekly group sessions)				✓			
Primary outcomes							
Recruitment and retention metrics	✓				✓	✓	✓
Intervention adherence (attendance)				✓	✓		
Acceptability (CSQ-8)					✓		
Intervention fidelity (audio coding)				✓			
Secondary outcomes							
Global cognition (BACS composite)		✓			✓	✓	✓
Functional capacity (UPSA-N)		✓			✓	✓	✓
Symptom severity (BPRS-18)		✓			✓	✓	✓
Disability (WHODAS 2.0)		✓			✓	✓	✓
Quality of life (MANSA, WHOQOL-BREF)		✓			✓	✓	✓
Social cognition (SCSQ-N)		✓					✓
Economic outcomes							
Resource use (CSRI)		✓					✓
Health utility (EQ-5D-5L)		✓					✓
Qualitative evaluation							
Interviews/ focus groups					✓		

BACS, Brief Assessment of Cognition in Schizophrenia; BPRS-18, Brief Psychiatric Rating Scale-18; CCT, compensatory cognitive training; CSQ-8, Client Satisfaction Questionnaire-8; CSRI, Client Service Receipt Inventory; EQ-5D-5L, EuroQol Five Dimensions Five Levels; MANSA, Manchester Short Assessment of Quality of Life; MINI, Mini-International Neuropsychiatric Interview; SCSQ-N, Social Cognition Screening Questionnaire-Nigeria; SPIRIT, Standard Protocol Items: Recommendations for Interventional Trials; UPSA-N, UCSD Performance-Based Skills Assessment; WHODAS 2.0, WHO Disability Assessment Schedule 2.0; WHOQOL-BREF, WHO Quality of Life-BREF.

The primary purpose of the trial is not to establish definitive clinical effectiveness, but rather to generate robust evidence on feasibility, acceptability, fidelity and preliminary outcome signals necessary to justify and inform a future definitive trial. The inclusion of a mixed-methods process evaluation allows for systematic examination of how the intervention is delivered in practice, the mechanisms through which it may exert effects, and the contextual factors that shape implementation within Nigerian public mental health services. In parallel, an exploratory health economic component is incorporated to estimate intervention delivery costs and patterns of service utilisation, supporting early assessment of scalability and affordability. The overall conceptual framework, mapping inputs, implementation metrics and mechanisms to primary and secondary outcomes, is presented in figure 2.

**Figure 2 F2:**
[figure not shown]
Conceptual framework linking adaptation, implementation processes, mechanisms and outcomes in the CognIFied pilot trial. BACS, Brief Assessment of Cognition in Schizophrenia; CSQ-8, Client Satisfaction Questionnaire-8; UPSA, UCSD Performance-Based Skills Assessment; YPAR, Youth Participatory Action Research.

#### Study setting

The study will be conducted across three major tertiary public psychiatric hospitals located in Lagos and Ogun States in South-West Nigeria. These facilities were purposively selected on the basis of their high patient volumes, established outpatient services for psychotic disorders, and existing research infrastructure capable of supporting longitudinal clinical trials. Each site also employs psychiatric social workers who are embedded within routine care teams, making them suitable candidates for task-shifted delivery of the intervention.

The participating sites are:

**Lagos State University Teaching Hospital (LASUTH), Ikeja**, a large general teaching hospital with a dedicated psychiatry department providing outpatient and inpatient mental health services.**Federal Neuro-Psychiatric Hospital, Yaba (FNPHY**), one of the busiest specialist psychiatric facilities in Nigeria, managing a high volume of individuals with psychotic disorders annually.**Neuropsychiatric Hospital Aro (NPHA), Abeokuta**, a specialist psychiatric hospital and designated WHO Collaborating Centre with longstanding involvement in mental health research and training.

Recruitment will take place primarily through outpatient clinics and early psychosis service streams within these hospitals. All intervention sessions will be delivered in existing group therapy rooms at the participating sites, ensuring that the study remains embedded within routine service environments and enhancing the ecological validity of findings.

### Participants and eligibility criteria

#### Target population

The trial will recruit 180 young adults aged 18–30 years with a diagnosis of FEP and evidence of objective cognitive impairment. Participants will be drawn from the outpatient departments of the three collaborating hospitals.

#### Inclusion criteria

Participants must meet all of the following criteria to be eligible for inclusion:

Aged between 18 and 30 years at the time of enrolment.Diagnosis of a primary psychotic disorder according to DSM-5 criteria.Onset of first psychotic episode within the previous 5 years, confirmed using the Mini-International Neuropsychiatric Interview (MINI V.7.0).^38^Objective cognitive impairment, defined as a composite score at least one SD below age-adjusted and education-adjusted normative means on the Brief Assessment of Cognition in Schizophrenia (BACS).^33^Sufficient proficiency in English or Nigerian Pidgin English to participate meaningfully in group sessions and assessments.Capacity to provide written informed consent, assessed using structured teach-back methods.Clinical stability, operationalised as no psychiatric hospital admission within the preceding 4 weeks and no major change in antipsychotic dosage within the preceding 2 weeks.Current engagement in outpatient care at one of the participating study sites.

#### Exclusion criteria

Participants will be excluded if they meet any of the following criteria:

Primary diagnosis of intellectual disability (estimated premorbid IQ <70), dementia or significant neurological disorder, including moderate to severe traumatic brain injury.Current substance dependence (excluding nicotine or caffeine), as defined by DSM-5 criteria.High and imminent risk of suicide or violence, or acute psychopathology requiring inpatient admission.Severe medical illness or uncorrected sensory impairment that would preclude regular attendance or participation.Concurrent participation in another psychosocial intervention trial or receipt of structured cognitive remediation therapy within the previous 12 months.

### Recruitment strategy

Participant recruitment is planned over a 9-month period, from 1 February 2026 to 30 November 2026, using a consecutive sampling approach. This strategy is intended to minimise selection bias while ensuring that the recruited sample reflects the clinical diversity of young people with FEP attending public psychiatric services.

Multiple, complementary recruitment pathways will be employed. Treating psychiatrists, nurses and psychiatric social workers will identify potentially eligible patients during routine outpatient visits and provide brief verbal information about the study. In addition, trained Youth Research Assistants (YRA) who are young people with lived experience of psychosis and have received training in research ethics and engagement will support recruitment by making initial approaches using culturally adapted information sheets available in English and Nigerian Pidgin English.

Eligibility screening will occur in two stages. First, diagnostic eligibility will be confirmed using the MINI V.7.0. Second, cognitive eligibility will be assessed using the BACS. Individuals who meet all eligibility criteria will be invited to provide informed consent prior to baseline assessment.

#### Informed consent procedure

Written informed consent will be obtained from all participants before any study-specific procedures are initiated. Recognising the potential impact of cognitive impairment on comprehension and decision-making, the consent process has been designed to be iterative and supportive. Research assistants will use structured teach-back methods, asking participants to explain key elements of the study, including its purpose, procedures, risks and voluntary nature, in their own words.

Participants will be given a minimum of 24 hours to consider participation and are encouraged to consult with family members or trusted individuals if they wish. Transport costs associated with screening and consent visits will be reimbursed. Only participants who demonstrate adequate understanding and voluntary agreement will be enrolled.

### Sample size and pilot rationale

The target sample size is 180 participants, with 90 allocated to each trial arm. In keeping with established guidance for pilot and feasibility trials, the sample size has been selected to provide adequate precision around key feasibility parameters rather than to ensure statistical power for hypothesis testing of clinical outcomes.

Assuming a conservative retention rate of 70%–75% at the 12-month follow-up, a sample of 180 participants allows estimation of retention with a 95% CI width of approximately ±7%. This level of precision is sufficient to apply prespecified ‘traffic light’ progression criteria to inform decisions regarding advancement to a definitive trial.

Although the study is not powered for definitive efficacy analyses, the planned sample size is expected to be sufficient to detect preliminary clinical signals. With 90 participants per arm, allowing for attrition, the study retains approximately 80% power at a two-sided alpha level of 0.05 to detect a medium effect size (Cohen’s d=0.50) on the BACS composite score. This calculation accounts for clustering effects associated with group-based intervention delivery, assuming an intraclass correlation coefficient (ICC) of 0.05.

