#### Intervention structure and delivery

The adapted CCT intervention consists of 12 weekly group sessions, each lasting between 60 and 90 min. A detailed overview of the curriculum content is provided in online supplemental file 1. Sessions are delivered to groups of six to eight participants to balance opportunities for peer interaction with individualised support. All sessions are conducted in designated group therapy rooms within participating hospitals, embedding the intervention within routine service settings.

Each session follows a standardised structure to promote consistency and skill consolidation. Sessions begin with a brief welcome and review of the session agenda, followed by discussion of homework assignments from the previous week. Core content is introduced through brief didactic teaching and live demonstrations, after which participants engage in guided practice exercises, including role-plays and problem-solving activities tailored to their own daily challenges. Sessions conclude with the collaborative assignment of personalised homework tasks designed to encourage real-world application of strategies.

Participants receive a printed workbook containing session summaries, worksheets and practical exercises, as well as wallet-sized cue cards highlighting key strategies.

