#### Structural equivalence

To ensure comparability, ERT is matched to the CCT intervention on key structural parameters. Participants attend 12 weekly group sessions of 60–90 min duration, delivered in groups of six to eight participants within the same hospital facilities. Sessions are scheduled with similar frequency and duration, and participants receive identical transportation reimbursement and refreshments. Sessions are facilitated by health educators or psychiatric social workers who are not involved in delivering CCT. Facilitators receive orientation to the control protocol to ensure consistency and to prevent inadvertent introduction of cognitive techniques.

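### The stated 80% power for d = 0.50 does not follow from the protocol's own inputs: attrition and clustering together leave about 67–76% for an unadjusted comparison

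*Protocol article*

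**What the plan says.** All of the following is in the Protocol article.

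- **Sample size and pilot rationale**, size: "The target sample size is 180 participants, with 90 allocated to each trial arm". The number is justified by precision for feasibility parameters, and the section says that the study is not powered for definitive efficacy.
- **Same section**, retention: "Assuming a conservative retention rate of 70%–75% at the 12-month follow-up". This stands in the paragraph on the width of the retention interval.
- **Same section**, power: starting from 90 per arm and with drop-out taken into account, "the study retains approximately 80% power at a two-sided alpha level of 0.05 to detect a medium effect size", specified as d = 0.50 on the BACS composite. The next sentence reads "This calculation accounts for clustering effects associated with group-based intervention delivery, assuming an intraclass correlation coefficient (ICC) of 0.05".
- **Intervention structure and delivery** (CCT): "Sessions are delivered to groups of six to eight participants".
- **Structural equivalence** (control): sessions are "delivered in groups of six to eight participants within the same hospital facilities". Both arms are therefore clustered.
- **Analysis of secondary outcomes**: the contrast of main interest is at 12 months, from a mixed model with random intercepts for participants and therapy groups, adjusted for the baseline value, site and age stratum.

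**The concern.** One power figure is said to carry two reductions, one for drop-out and one for clustering by therapy group. A standard calculation reaches 80% with the first reduction alone, so the second seems to be claimed but not applied.

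This is the only power figure in the article, and it supports the statement there that the sample should be large enough to pick up preliminary clinical signals. If it is too high, a flat BACS result would be read against more sensitivity than was shown. A team planning the definitive trial might also take over a calculation that leaves out the design effect.

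**Working it through.** **Inputs.** 90 per arm; two-sided alpha 0.05; d = 0.50; ICC 0.05; retention r = 0.70 to 0.75; group size m = 6 to 8 in both arms. Retention and group size come from other paragraphs than the power sentence. Using the 12-month retention is an inference, and it rests on the contrast of interest being at 12 months.

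**Formulas.**
- Design effect: DEFF = 1 + (m − 1) × 0.05, with m either the planned group size or the retained group size m × r.
- Effective number per arm: n_eff = 90 × r / DEFF.
- Power: two-sample t test, non-centrality d × √(n_eff / 2), 2·n_eff − 2 degrees of freedom.

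**Step 1: can the stated figure be reproduced?**

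| Adjustment | n_eff per arm | Power |
|---|---|---|
| None | 90 | 91.6% |
| Attrition only, r = 0.70 | 63 | 79.5% |
| Attrition only, r = 0.75 | 67.5 | 82.2% |
| Clustering only, m = 6 (DEFF 1.25) | 72.0 | 84.6% |
| Clustering only, m = 7 (DEFF 1.30) | 69.2 | 83.2% |
| Clustering only, m = 8 (DEFF 1.35) | 66.7 | 81.7% |

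The closest match to 80% is attrition alone at 70% retention.

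**Step 2: both adjustments together, as the text claims.** Worked example for r = 0.70, m = 7, planned size: DEFF = 1 + 6 × 0.05 = 1.30; n_eff = 63 / 1.30 = 48.5; power 68.3%.

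| r | m | DEFF (planned) | n_eff | Power | DEFF (retained) | n_eff | Power |
|---|---|---|---|---|---|---|---|
| 0.70 | 6 | 1.25 | 50.4 | 70.0% | 1.16 | 54.3 | 73.3% |
| 0.70 | 7 | 1.30 | 48.5 | 68.3% | 1.195 | 52.7 | 72.0% |
| 0.70 | 8 | 1.35 | 46.7 | 66.6% | 1.23 | 51.2 | 70.7% |
| 0.75 | 6 | 1.25 | 54.0 | 73.1% | 1.175 | 57.4 | 75.7% |
| 0.75 | 7 | 1.30 | 51.9 | 71.3% | 1.2125 | 55.7 | 74.4% |
| 0.75 | 8 | 1.35 | 50.0 | 69.7% | 1.25 | 54.0 | 73.1% |

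The range is 66.6% to 75.7%. The normal approximation gives 67.6% to 76.4%, so the choice of test does not explain the gap. The type II error is about 24–33%, against the implied 20%.

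**Step 3: effect detectable at 80% power.** Solving the same formula for d gives 0.527 at n_eff = 57.4 and 0.586 at n_eff = 46.7, so about 0.53 to 0.59.

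**Step 4: other readings (normal approximation).**
- Clustering in the CCT arm only: 73.5% to 79.5%. The control arm is also delivered in groups, so this reading does not apply.
- One-sided 0.05: 77.9% to 85.0%. The text says two-sided.

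**Step 5: baseline adjustment.** With a baseline-to-12-month correlation ρ, and d on the unadjusted SD, the residual variance is multiplied by 1 − ρ², so n_eff becomes n_eff / (1 − ρ²). Power of 80% then needs ρ of about 0.31 in the best case (r = 0.75, m = 6, retained size) and about 0.52 in the worst (r = 0.70, m = 8, planned size). The normal approximation gives 0.29 and 0.51. By t test, power is 71–80% at ρ = 0.3 and 79–87% at ρ = 0.5. The article gives no value of ρ, so these are assumptions that show the range.

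**The case against.** The strongest reply is that the planned test is not the unadjusted comparison computed here. The analysis section specifies a mixed model adjusted for the baseline value, and the theoretical rationale for CCT describes cognitive impairment in psychosis as fairly stable over time, which makes a useful correlation plausible. At ρ = 0.5 the planned model would have roughly 80% power or more in nearly every scenario. This stands. A reader might infer from the tables that the trial cannot deliver 80% power. The documents do not support that reading, because the shortfall is shown for the calculation as described and not for the planned model.

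Second, the power sentence names no attrition rate and no group size. That is also true. The 70–75% is taken from the preceding paragraph and the group sizes from the intervention sections. The inference is sound, since the contrast is at 12 months and no other retention figure is offered. That clustering was left out is likewise only suggested by the match at 70% retention.

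Third, this is a pilot. The sample size rests on feasibility precision, p values are to be read cautiously, effects are reported with intervals, and no progression criterion uses the BACS. This limits the consequence but does not make the figure right.

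Finally, an article may leave the details of a power calculation to a fuller document. The point here is not an omission: the article states a number and says what it includes, and its own inputs give a different one.

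**Conclusion.** The concern holds for the statement as written. On the article's inputs, with both claimed adjustments applied, power for d = 0.50 is about 67–76% and not about 80%, and 80% power applies to d of about 0.53–0.59. This rests on 70–75% retention at 12 months, groups of six to eight in both arms, the standard design effect at ICC 0.05, and no gain from baseline adjustment. Such a gain could bring power back to 80% if ρ is at least about 0.3 to 0.5, depending on the scenario, but the power statement does not claim it.

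A reader might go further and conclude that the sample is too small. The documents do not support that, since the number was not chosen for efficacy. Severity is moderate to minor: the error affects how an exploratory result is read, and no feasibility conclusion or progression decision.

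**What to change.** Revise the power paragraph in one of two ways.

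1. Restate the figure: with 63–67.5 per arm at 12 months, groups of six to eight in both arms and an ICC of 0.05, an unadjusted comparison has about 67–76% power for d = 0.50, and 80% power for d of about 0.53–0.59.
2. If baseline adjustment was part of the calculation, say so, and give the retention, the group size and the baseline-to-12-month correlation that yield 80%, with the source of that correlation.

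The cost is one paragraph of text and, under the first option, a less favourable number. The sample size, design and analysis stay as they are.
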